### Sample size

Our sample size of 314 (figure 1) is expected to provide 90% ‘intention-to-treat’ and 80% ‘per-protocol’ study power to detect a 27.5% relative reduction^11^ in new ARI episodes between those receiving vitamin D supplementation (2.54/year) compared with placebo (3.50/year). Power calculations are based on local ARI rates,^3 8 49^ 14% non-compliance, 3% lost to follow-up and assume the outcome data fit a negative binomial distribution (dispersion factor, k=0.4).^50^ Our RCT’s predicted effect size is consistent with a similar New Zealand study by Grant *et al*.^11^ We expect a low drop-out rate because the primary outcome is informed by passively collected medical record data for each child.

### Assignment of interventions

#### Sequence generation

Sequential randomisation codes were computer-generated using permuted blocks (two blocks of differing sizes), stratified by community (urban and remote). The allocation ratio within these strata is 1:1 (vitamin D: placebo). There is one random allocation per mother–infant pair.

#### Allocation concealment

An independent study statistician generated the randomisation codes. Medication bottles are labelled by an independent clinical pharmacist from Royal Darwin Hospital. Labels incorporate a clear specification for mother or infant to avoid mix-up. Sequentially labelled mother and infant bottle pairs are stored in strata-specific boxes at room temperature in a secure facility. Active and placebo study medicine bottles and administration syringes are identical. Liquid medicines are indistinguishable in appearance and taste.

#### Allocation implementation

Good Clinical Practice (GCP) trained research nurses or First Nations health practitioners allocate the study medicine to each mother–infant pair by selecting the next sequentially labelled (prerandomised) study medication from the appropriate stratification group. The allocation sequence number is recorded by the research team on the data collection form (DCF), the database and in the participant’s medical record. Infants receive the same allocation as their mother.

#### Blinding

The study is double-blinded. All investigators, participants, carers, hospital and clinic staff are blinded to the treatment group until completion of study follow-up. Unblinding is permissible if the independent data safety monitoring committee (iDSMC), principal investigator or appropriate qualified delegate is compelled by evidence of a safety concern.

### Data collection, management and analysis

#### Data collection methods

All study visit and clinical data are recorded by research nurses on standardised paper-based DCFs. Protocol adherence (deviations/violations) are continuously monitored and documented by study staff. Established methods are used to document episodes of respiratory infection from medical records.^33–35^ Collection and processing times, and quality measures are recorded for all biological samples. A GCP compliant protocol is employed if corrections are made to paper-based records. All study documents are securely retained at MSHR.

#### Sample collection

Established methods are being used for the collection and processing of blood, breast milk, nasal, stool and saliva samples.^4 34 35 42 51^ Briefly, whole cord blood is collected via venepuncture: (1) into three (10 mL) heparinised tubes containing an equal volume of RMPI (Sigma-Aldrich) cell culture media; (2) into heparinised paediatric blood tubes (<1 mL) and (3) onto Guthrie cards (~80 µL). Maternal and infant venous bloods (finger or heel prick) are collected first onto Guthrie cards (filling designated spot to the edge) and then into heparinised tubes if the volume is sufficient. The cord blood samples collected in media are kept at room temperature and an aliquot is used for immunophenotyping^43^ prior to isolation of CBMCs. Plasma is obtained from all other heparinised blood samples following centrifugation. Guthrie card samples are dried for 24 hours then stored as DBS in an envelope at room temperature. Nasal samples are collected with a sterile wire shafted swab (Copan) then placed into skim milk-tryptone-glucose-glycerol broth. All samples (except cord blood-media samples and DBS) are kept at 4°C during processing. Isolated CBMCs and samples (except DBS) are stored in cryotubes at −80°C within 24 hours of collection.

#### Data management

Data are entered by the research nurses into a REDCap electronic data capture (EDC) tool with web-based interface,^52 53^ hosted by MSHR at Charles Darwin University. Laboratory data are entered by the laboratory scientist. The EDC tool includes built-in validation ranges to facilitate accurate data entry. An EDC audit trail maintains a record of entries and changes made. Logic and 10% data checks (EDC cross-checked with DCFs) are performed regularly. Error rates greater than 1% precipitate 100% checks of targeted data fields and further 10% checks of all data.

#### Statistical analyses

The RCT is being conducted and reported according to CONSORT (Consolidated Standards of Reporting Trials) guidelines.^54^ A detailed statistical analysis plan will be developed by the investigators and study statisticians prior to the unblinding and final analysis.

The primary ‘intention-to-treat’ analysis will compare the incidence of infant ARI (episodes/child/12 months) between active and placebo groups using a negative binomial regression model and producing an estimate of the incidence rate ratio (IRR) with 95%CIs. The model will include terms to account for repeat mothers and twins. There will be no imputation for missing data. Supplementation efficacy will be defined as (1−IRR)×100.

Secondary analyses (clinical) will include between group comparisons of (1) the proportion of children having any ARI episode <12 months (using a generalised linear model with effects presented as risk ratios), (2) time to first ARI presentation (using Cox regression with effects presented as HRs) and (3) the incidence of ARI subgroup outcomes (pneumonia, bronchiolitis and OM using negative binomial regression with effects presented as IRRs). Sensitivity analyses will include those (1) with hospitalised outcomes and (2) clinical outcomes requiring antibiotics. A per-protocol analysis (excluding those who missed >3 consecutive doses) will also be conducted for all clinical outcomes.

Secondary analyses (biological) will compare between-group differences in (1) circulating vitamin D levels: mean plasma 25OHD at each visit and breast milk 25OHD at birth (Student’s t-test), (2) microbiological outcomes: proportions of nasal swabs positive for *S. pneumoniae*, NTHi and RSV using χ^2^ tests and reporting risk ratios with 95% CIs and (3) immune function measures: median immune cell population counts in cord blood at birth and infant blood at 4 months; median circulating inflammatory marker levels in cord blood at birth and infant blood at 4 months; median CBMC population counts and CBMC challenge-induced cytokine levels (Wilcoxon rank-sum test); geometric mean concentrations of IgG and IgA to pertussis vaccine antigens in maternal plasma and breast milk; geometric mean concentrations of IgG and IgA PCV serotype antigens (five types) in infant saliva and plasma at age 4 months (Student’s t-test). All data will be analysed using Stata Statistical Software: Release V.17 (StataCorp) and GraphPad Prism V.9 (GraphPad Software, USA).

For all analyses, p values <0.05 will be considered statistically significant. No adjustments will be made for multiple comparisons.

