**Methods and analysis:**

‘D-Kids’ is a parallel (1:1), double-blind (allocation concealed), randomised placebo-controlled trial conducted among NT First Nations mother–infant pairs. Pregnant women and their babies (n=314) receive either vitamin D or placebo. Women receive 14 000 IU/week or placebo from 28 to 34 weeks gestation until birth and babies receive 4200 IU/week or placebo from birth until age 4 months. The primary outcome is the incidence of ARI episodes receiving medical attention in the first year of life. Secondary outcomes include circulating vitamin D level and nasal pathogen prevalence. Tertiary outcomes include infant immune cell phenotypes and challenge responses. Blood, nasal swabs, breast milk and saliva are collected longitudinally across four study visits: enrolment, birth, infant age 4 and 12 months. The sample size provides 90% power to detect a 27.5% relative reduction in new ARI episodes between groups.

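### The primary negative binomial model names terms for repeat mothers and twins but not the urban/remote randomisation stratum; if community predicts ARI, the interval is conservative and some power is forgone

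*Protocol article*

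**What the plan says.** Under Sequence generation, the protocol article says that allocation uses "permuted blocks (two blocks of differing sizes), stratified by community (urban and remote") and adds: "The allocation ratio within these strata is 1:1 (vitamin D: placebo"). Community is the only stratification factor.

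Under Statistical analyses, the primary intention-to-treat comparison of ARI incidence is made "using a negative binomial regression model and producing an estimate of the incidence rate ratio (IRR) with 95%CIs". The next sentence reads: "The model will include terms to account for repeat mothers and twins". Urban/remote is not named as a term there or anywhere else in the analysis text. The listed Cox, risk-ratio and subgroup analyses carry no stated covariates.

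The same section also says: "A detailed statistical analysis plan will be developed by the investigators and study statisticians prior to the unblinding and final analysis".

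**The concern.** Stratified blocks force community to be balanced between the arms. If infants in remote and urban communities have different ARI rates, that balance removes part of the chance variation in the treatment comparison. A model without the stratum does not recognise this. It treats the difference between strata as extra unexplained variation, the estimated dispersion rises, and the reported standard error of the log IRR exceeds the estimator's true sampling variability.

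The article describes its primary model down to individual terms. It names those for twins and previously enrolled mothers, who according to the Discussion were brought in to counter slow recruitment, but not the factor built into the randomisation. A SAP that copied this sentence would carry the mismatch into the final analysis. At stake is precision on the primary outcome, in a trial that had recruited 184 infants by December 2022 and reports that pandemic measures lowered ARI rates.

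**Working it through.** **Inputs from the protocol article.** Sample size: 314 in total, 90% intention-to-treat power, 3.50 episodes/year on placebo and 2.54 on vitamin D, negative binomial with k = 0.4, 3% lost to follow-up. Statistical analyses: p < 0.05, taken as two-sided because 95% intervals are reported. Trial design and setting: about 70% of NT First Nations families live remotely. This is a population figure and is used here as an assumption for the trial sample.

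**Not in the documents, so assumed over a range:** the remote:urban ARI rate ratio, and the remote share of the trial sample.

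**Step 1: reproduce the plan's figure.** With variance = μ + kμ²:

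n per arm = (1.960 + 1.282)² × (1/3.50 + 1/2.54 + 2 × 0.4) / [ln(2.54/3.50)]² = 10.507 × 1.4794 / 0.10278 = 151.2

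This rounds up to 152 per arm, or 304 evaluable, and 304 / 0.97 = 313.4, which rounds up to the stated 314. At 152 per arm, SE(log IRR) = √(1.4794/152) = 0.0987 and power = Φ(0.3206/0.0987 − 1.960) = 90.1%. The formula has no stratum term, so the stated power does not depend on adjustment.

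**Step 2: split the overall dispersion.** Keep the overall k at 0.4. With CV² the squared coefficient of variation of the stratum means, the within-stratum dispersion is

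k_within = (0.4 − CV²) / (1 + CV²)

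**Step 3: worked case, 70% remote, rate ratio 2.**
- On a scale where the urban mean is 1, the overall mean is 0.7 × 2 + 0.3 × 1 = 1.7 and the mean square is 0.7 × 4 + 0.3 × 1 = 3.1. So CV² = 3.1/1.7² − 1 = 0.073 and k_within = 0.327/1.073 = 0.305.
- Placebo means are 3.50/1.7 = 2.06 (urban) and 4.12 (remote).
- The variance of the log IRR in each stratum is (1/μ + 1/(0.7257μ) + 2 × 0.305)/n. Urban (n = 45.6 per arm) gives 0.0387 and remote (n = 106.4) gives 0.0112.
- The pooled SE is 1/√(1/0.0387 + 1/0.0112) = 0.0931. Power is Φ(0.3206/0.0931 − 1.960) = 93.1%.
- The unadjusted SE is 0.0987/0.0931 = 1.06 times as large.

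**Step 4: the range (304 evaluable, 70% remote).**

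| Rate ratio | k within | SE unadjusted | SE adjusted | Unadjusted wider by | Power unadjusted | Power adjusted |
|---|---|---|---|---|---|---|
| 1 | 0.400 | 0.0987 | 0.0987 | 0% | 90.1% | 90.1% |
| 1.25 | 0.387 | 0.0987 | 0.0979 | 0.8% | 90.1% | 90.6% |
| 1.5 | 0.361 | 0.0987 | 0.0964 | 2.4% | 90.1% | 91.4% |
| 2 | 0.305 | 0.0987 | 0.0931 | 6.0% | 90.1% | 93.1% |
| 3 | 0.222 | 0.0987 | 0.0878 | 12.4% | 90.1% | 95.5% |

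At rate ratio 2, a 50% or 30% remote share gives 9.5% or 10.9% wider, with adjusted power 94.5% or 95.0%. At rate ratio 3 the same shares give 23.7% or 34.5% wider.

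**Step 5: simulation check.** 1000 trials per setting, stratified 1:1 allocation, 70% remote, maximum-likelihood negative binomial fits:

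| Rate ratio | Type I error unadjusted / adjusted | Power unadjusted / adjusted |
|---|---|---|
| 1 | 5.0% / 4.8% | 90.5% / 90.4% |
| 1.5 | 5.0% / 5.5% | 90.6% / 91.1% |
| 2 | 3.2% / 4.4% | 92.4% / 94.1% |
| 3 | 2.2% / 4.4% | 92.5% / 95.8% |

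The Monte Carlo standard error is about 0.7 points at 5% (√(0.05 × 0.95/1000)) and 0.9 at 90%. At rate ratio 3 under the null, the unadjusted model reported a mean SE of 0.096 against an empirical SD of 0.084, which shows the overstatement directly. Simulated power gains are smaller than the formula's (1.7 and 3.3 points at ratios 2 and 3, against 3.0 and 5.4), because stratified allocation also reduces the true variability of the unadjusted estimate.

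**The case against.** The strongest reply is that silence is not exclusion. The article does not say that its list of terms is complete, a SAP is still to be written, and a covariate list is the kind of detail that a condensed article leaves to it. This stands in part. A reader might infer that the plan has decided against adjusting for community, and the text does not support that. But the model has been described at the level of terms, and in that form it is less efficient than one that follows the randomisation whenever community is prognostic.

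A reader might also infer that the trial will miss its 90% power, or that the primary test is invalid. Neither follows. The 314 reproduces from a formula with no stratum, so what is forgone is an extra gain. Unadjusted type I error was at or below 5% in every simulated setting, and nothing here shows bias in the IRR.

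Third, the loss is conditional. With no urban/remote difference it is zero, at a rate ratio of 1.25 it is under 1% in SE, and material effects need ratios of about 2 to 3. The documents give no figure that places the trial in that range. An SE reduction of about 20% can be obtained at rate ratio 3 by assuming half the sample is remote. At the only share the documents offer, the unadjusted SE is 12.4% wider, which is a reduction of about 11% (1 − 1/1.124). All of this stands.

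Finally, the dispersion argument is specific to negative binomial regression. It does not carry over to the Cox or risk-ratio models, and no calculation here covers them.

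**Conclusion.** The point holds as a conditional loss of efficiency. The primary model as described does not name the one factor used to stratify allocation. Used as written, it gives a conservative interval for the IRR to the extent that community predicts the ARI rate.

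On the assumptions above, the cost in SE runs from nothing to about 12% across rate ratios of 1 to 3 at 70% remote, and is larger at the lower shares examined. The corresponding power gain from adjusting is 0 to about 5 points by formula and somewhat less in simulation. Where the trial falls in that range is unknown, because neither the stratum rates nor the trial's own remote share is given. Adjustment costs essentially nothing if the stratum turns out not to matter, since both models then have an SE of 0.0987. This is therefore a free improvement to make and does not invalidate the planned analysis.

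**What to change.** Before unblinding, state in the SAP that the primary negative binomial model contains treatment arm and community stratum (urban/remote, as used at randomisation) as fixed effects, together with the terms for repeat mothers and twins. Use the same specification for the negative binomial models of pneumonia, bronchiolitis and otitis media.

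The stratum can also be added to the Cox and risk-ratio models for consistency with the randomisation, but the SE figures given here should not be quoted for them.

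The cost is wording plus one covariate already recorded for every mother–infant pair at allocation. No new data and no change to the sample size are needed, and because the SAP precedes unblinding the choice cannot be influenced by results.

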### Intervention

Eligible mother–infant pairs are randomised with equal probability to receive either weekly vitamin D (coconut oil plus cholecalciferol) or placebo (coconut oil only).

Both liquid active and placebo study medicines are manufactured and supplied by Ddrops, Ontario, Canada. Ddrops recommends storage in an upright position between 5°C and 30°C though the product has passed long term stability tests at 40°C. Stock medicine bottles and prefilled syringe doses (capped and placed in a labelled envelope) were both stored in the Menzies School of Health Research (MSHR) pharmacy at ambient temperature (approximately 21°C) prior to dosing. Mothers who received doses for self-administration were instructed to keep them in a secure, unrefrigerated location inside their house.

The maternal vitamin D dose is 14 000 IU/week (equivalent to 2000 IU/day); the infant dose is 4200 IU/week (equivalent to 600 IU/day). Mothers vitamin D or placebo commences at enrolment (28^+0^ to 34^+6^ weeks gestation) and continues until delivery (table 1, figure 1). Infant vitamin D or placebo commences at birth and continues until 4 months of age. Infants discharged from hospital with a recommendation to take oral vitamin D (400 IU/day) receive a reduced vitamin D dose of 3000 IU/week (equivalent to 430 IU/day).

**Table 1 T1:** Participant timeline

Study visit:	0	1	2	3	4
Gestation (weeks)/infant age (months)*	20^+0^–27^+6^	28^+0^–34^+6^	0	4	12
Enrolment:					
Eligibility screen	✓	✓			
Informed consent/random allocation		✓			
Intervention:					
Mother (vitamin D or placebo)		✓	✓		
Infant (vitamin D or placebo)			✓	✓	
Primary outcome:					
Incidence of medically attended ARI episodes†			✓	✓	✓
Secondary outcomes:					
Clinical					
Prevalence of ≥1 medically attended ARI episode			✓	✓	✓
Time to first medically attended ARI episode			✓	✓	✓
Incidence of (1) pneumonia, (2) bronchiolitis, (3) otitis media			✓	✓	✓
Biological					
Vitamin D levels (circulating 25OHD_3_ concentration)		✓	✓	✓	✓
Systemic immunology (phenotype, CBMC challenge, vaccine Ig’s)			✓	✓	
Nasal microbiology (bacterial and viral pathogen prevalence)				✓	✓

*Window for visit 2 or birth visit: 0–14 days; visit 3 or 4-month visit: 3.5–6 months; visit 4 or 12-month visit: 11–18 months.

†Hospital or primary healthcare presentation.

ARI, any acute respiratory infection; CBMC, cord blood mononuclear cells; 25OHD, 25-hydroxy-vitamin D.

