#### Secondary outcomes

Pneumonia, bronchiolitis and OM (incidence) will be analysed as specific ARI subgroups (online supplemental material 1). Hospitalisation, antibiotic and oxygen therapy will be used as measures of severity.

Circulating 25OHD concentrations are measured in maternal blood at baseline (≤34^+6^ weeks) and at birth, in cord blood, and in infant blood at birth, 4 and 12 months, using high-performance liquid chromatography (HPLC) as described previously.^36 37^ Blood samples for vitamin D analysis include both plasma and dried blood spots (DBS). DBS-based 25OHD concentrations will be adjusted for haematocrit as necessary.^38^ Vitamin D levels <50 nmol/L are considered deficient.

The prevalence of nasal pathogens will be determined via nasal swabs, collected from infants at ages 4 and 12 months. Swabs will be screened for key respiratory bacteria (*Streptococcus pneumoniae*, non-typeable *Haemophilus influenzae* (NTHi)) and viruses (RSV) using WHO culture^39^ and standardised RT-PCR methods, respectively.^40 41^

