Visit 1, enrolment: Pregnant mothers are eligible for enrolment at 28^+0^ to 34^+6^ weeks gestation. At this visit, we provide a detailed explanation of the study rationale and requirements using plain language study material (including a participant information sheet, pictorial flipchart and consent form). First Nations team members translate materials as necessary. Interested families are formally invited to participate in the study. With written informed consent and confirmation of eligibility, mothers are enrolled and randomly allocated to the intervention or placebo arm. A baseline blood sample is collected prior to supervised administration of the first dose of study medicine.

Visit 2, birth: At delivery, cord blood is collected by the attending obstetricians or midwives and transported to the laboratory for processing within 24 hours. Study staff visit mothers and their babies within 14 days of birth. The visit coincides with the end of the maternal supplementation. Blood and breast milk (at least 3 days post partum) are collected from mothers. Blood and saliva are collected from neonates. Infant study medicine is commenced, and the first dose is administered.

Visit 3, infant age 4 months: Families are visited when infants are 3.5–6 months of age, coinciding with the end of the infant supplementation period (16th week post partum). An infant blood, nasal swab and saliva sample are collected.

Visit 4, infant age 12 months: The final study visit occurs between infant ages 11–18 months. An infant blood and nasal swab are collected. Families receive a small thankyou gift for their contribution.

Routine data are collected at each visit, including personal, household and community demographics, medical and vaccination history, smoke exposure, time spent indoors and use of vitamin D or other supplements, breastfeeding status and infant growth metrics. Serious adverse events (SAEs) and clinical outcomes are monitored via maternal and infant medical records (hospital and primary care) throughout follow-up.

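### 25OHD is compared by unadjusted t-tests at every visit, which forgoes precision available from data already collected and, read literally, tests the pre-dose value

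*Protocol article*

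**What the plan says.** All references are to the protocol article.

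- **Statistical analyses:** "Secondary analyses (biological) will compare between-group differences in (1) circulating vitamin D levels", namely "mean plasma 25OHD at each visit and breast milk 25OHD at birth (Student’s t-test"). No covariate is named. The same section says that the primary negative binomial model will allow for twins and for mothers who enrol more than once. It also says that a detailed analysis plan will be written before unblinding.
- **Statistical analyses, closing lines:** "For all analyses, p values <0.05 will be considered statistically significant". "No adjustments will be made for multiple comparisons".
- **Secondary outcomes:** "Circulating 25OHD concentrations are measured in maternal blood at baseline" and at birth, in cord blood, and in infant blood at birth, 4 and 12 months. Both plasma and dried blood spots are used.
- **Study visits, visit 1:** "A baseline blood sample is collected prior to supervised administration of the first dose of study medicine".
- **Table 1:** the secondary-outcome row "Vitamin D levels (circulating 25OHD_3_ concentration") is ticked at four visits, the first of them enrolment. The footnote gives "visit 3 or 4-month visit: 3.5–6 months".
- **Sequence generation:** allocation is stratified by urban or remote community, with one allocation per mother–infant pair.
- **Eligibility criteria and Allocation implementation:** dichorionic twins and previously enrolled mothers may join, and infants take their mother's allocation, so twins are always in the same arm.

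**The concern.** Whether supplementation reduces vitamin D deficiency at birth and in infancy is the first of the secondary aims, and the 25OHD contrast is needed to interpret either a positive or a null result on respiratory infections. It should be estimated as well as the data allow.

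The stated test falls short in three ways.

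1. It leaves out a pre-dose measurement of the same analyte, and the stratification factor, both of which are already in the database.
2. It treats all infants as independent. The primary model, described in the same section, does not.
3. It applies to each visit. Because Table 1 counts enrolment among the 25OHD visits and the 0.05 threshold covers all analyses, a literal reading produces a significance test on blood taken before any study medicine. Under randomisation a difference there can only be chance, so the p value answers no useful question and has a 5% probability of appearing significant.

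**Working it through.** **Figures in the plan.** No sample size, standard deviation or correlation is given for 25OHD. The only stated figure is the total of 314 for the primary outcome, and it reproduces:

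- n per arm = (1.960 + 1.282)² × [(1/3.50 + 0.4) + (1/2.54 + 0.4)] / [ln(2.54/3.50)]² = 151.2, rounded up to 152.
- 2 × 152 = 304, and 304/0.97 = 313.4, i.e. 314.

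I use 314 below only as a scale.

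**Precision forgone.** For a linear model with one baseline covariate whose correlation with the outcome is ρ:

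- variance (adjusted) / variance (t-test) = 1 − ρ²
- SE multiplier = √(1 − ρ²)
- size at which a t-test would match the adjusted analysis of 314 = 314/(1 − ρ²)

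| Assumed ρ | Variance ratio | SE multiplier | Equivalent N |
|---|---|---|---|
| 0.1 | 0.99 | 0.995 | 317 |
| 0.2 | 0.96 | 0.98 | 327 |
| 0.3 | 0.91 | 0.95 | 345 |
| 0.5 | 0.75 | 0.87 | 419 |
| 0.7 | 0.51 | 0.71 | 616 |

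Only the mother has a pre-dose value. A useful ρ is therefore most plausible for maternal blood at birth, cord blood and the neonatal sample. For infant blood at 4 and 12 months, after the infant's own course of study medicine, the first two rows may be the realistic ones. The background section says that cord 25OHD averaged 48% below maternal 25OHD in an earlier local cohort, but a difference in means says nothing about ρ.

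**Does the loss matter for power?** With 157 per arm, the difference detectable by t-test with 80% power is (1.960 + 0.842) × √(2/157) = 0.32 SD, which is 6.3, 7.9 or 9.5 nmol/L at assumed SDs of 20, 25 or 30. With 130 samples per arm (assumed):

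| True difference (assumed) | SD (assumed) | t-test power | Power with adjustment, ρ = 0.5 |
|---|---|---|---|
| 10 nmol/L | 20 | 98% | 99.7% |
| 10 nmol/L | 25 | 90% | 96% |
| 10 nmol/L | 30 | 77% | 87% |
| 19 nmol/L | 20 to 30 | above 99.9% | not needed |
| 19 nmol/L | 40 | 97% | not needed |

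The 19 nmol/L is the gap between the two cord-blood means quoted in the background (56 and 37). It serves only as a scale and is not an expected treatment effect.

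**Twins and repeat mothers.** If a proportion p of infants belong to same-arm twin pairs, ignoring the pairing understates the variance by a factor of about 1 + p × ICC. The number of twins is not given. At an assumed p = 0.04 and the extreme ICC = 1, the factor is 1.04, and √1.04 = 1.02 on the standard error. Repeat mothers receive a separate allocation for each pregnancy and may fall in different arms, so ignoring that correlation need not make the standard error too small.

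**Age at sampling.** Infant dosing ends around week 16 and the 4-month window closes at 6 months, about week 26. Samples can therefore be taken up to about 26 − 16 = 10 weeks after dosing ends. This adds spread within each arm. With blinding and a common window, nothing suggests that it differs between arms.

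**The case against.** The strongest reply is that nothing here is an error. Under randomisation the unadjusted difference in means is unbiased, covariates for secondary outcomes are ordinarily settled in the analysis plan, and that plan is still to come. Power for moderate to large differences looks ample without adjustment. The baseline test is inferred by joining a condensed phrase to a tick in a timeline table. If it were run, it would yield one uninformative p value and change no treatment estimate.

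Most of this stands, and it sets the weight of the point. It does not remove it, because the protocol names a specific test and a better one is available at no cost in data.

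A reader might infer more than the documents support:

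- **That the pre-dose sample was taken to serve as a covariate.** The protocol gives its timing and states no such purpose.
- **That the t-test makes the 25OHD result invalid or the trial underpowered for it.** Omitting baseline causes no bias, and the power figures above do not show a shortfall except for a small assumed difference with a large assumed SD.
- **That clustering seriously distorts the standard errors.** The counts are not given, and the effect of twins is probably small.
- **That adjusting for age repairs the wide visit window.** It can absorb some spread, but it cannot restore exposure that has lapsed since dosing ended.

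Two practical objections need an answer in the fix. Under Sample collection, maternal finger-prick blood goes first onto cards and into tubes only if there is enough, so baseline plasma may often be missing. And the primary-analysis paragraph rules out imputation.

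**Conclusion.** The point holds as a minor efficiency and reporting improvement on a secondary outcome. The planned t-tests are unbiased but leave out an available pre-dose value and the stratification factor. The cost in precision is a standard error larger than necessary by a factor of 1/√(1 − ρ²), with ρ unknown. It could be material for samples taken at birth and close to nil at 4 and 12 months. The gain from the urban or remote stratum cannot be sized from the documents. The mismatch with the primary model over twins and repeat mothers is real but probably small in effect. The test of the pre-dose visit rests on a literal reading of the phrase about each visit together with Table 1, and should be ruled out in words. All correlations, SDs, differences, the 130 per arm and the twin proportion above are assumptions.

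**What to change.** In the analysis plan, before unblinding:

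1. Describe baseline maternal 25OHD by arm without a significance test.
2. Compare post-baseline 25OHD (maternal, cord and infant at birth; infant at 4 and 12 months) by linear regression on arm, maternal baseline 25OHD and urban or remote stratum, optionally with infant age at sampling. Cluster standard errors on mother. Report the adjusted mean difference with its 95% CI.
3. State whether the baseline covariate comes from plasma or from dried blood spots.
4. Where the baseline covariate is missing, use a simple fill or a missing indicator so that no participant is dropped. Say that this applies to the covariate only and that no outcome is imputed, so that it sits clearly beside the existing wording on missing data.

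The cost is a paragraph of text and a few lines of Stata. No new samples, visits or participants are needed.
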